### Intervention

Apart from the trial airway management method (LMA or ETI), other clinical decisions will be made by the practitioners at each site according to their clinical judgement and hospital protocol, including anesthesia induction, maintenance and recording, anesthetic drug use and dosage, surgical approach, and ICU treatment.

### Primary outcomes

The primary outcomes are the incidence of PPCs (diagnostic criteria shown in Tables 3 and 4) and perioperative mortality rate.

**Table 3 Tab3:** Classifications of PPCs

Grading	Definition
0	No pulmonary complications
1	Any one of the following: cough, minor lung atelectasis (no obvious cause), dyspnea (no obvious cause)
2	Cough and sputum production (no obvious cause), bronchospasm (new-onset asthma or exacerbation of existing asthma that requires treatment), hypoxemia (SpO2 < 90% or PaO2 < 60 mmHg while breathing air), atelectasis (diagnosed by radiography or abnormal pulmonary sign with T > 37.5), hypercapnia (temporary or requires treatment; caused by medication or over-ventilation)
3	Pleural effusion (that requires drainage), suspected pneumonia (indicated by radiography, with or without microbiologic findings), diagnosed pneumonia (diagnosed based on the combination of radiology finding and microbiology evidence such as Gram staining or culture), pneumothorax (suggested by X-ray: observation of a lucent gas space devoid of pulmonary vessels between visceral pleura and the parietal pleura or symptoms of dyspnea, chest pain, irritating cough), noninvasive or invasive mechanical ventilation < 48 h
4	Respiratory failure (that requires noninvasive or invasive mechanical ventilation for > 48 h)

*PaO2* partial pressure of oxygen, *SpO2* blood oxygen saturation, *T* body temperature

**Table 4 Tab4:** Definition of PPCs

Complications	Diagnostic criteria
Pneumonia	X-ray finding of a new or progressive pulmonary infiltration and meeting 2 of the following 3 indications:
	(1) Cough, exacerbation of dyspnea or purulent sputum
	(2) Body temperature above 38 °C or under 36 °C
	(3) WBC > 12,000 or < 4000/μL
Atelectasis	Mainly based on X-ray findings as follows:
	Lung collapse
	Compensatory hyperinflation of adjacent ipsilateral lung tissue
	Wedge- or linear-shaped opacities
	Shifting of mediastinum
	Diaphragm move towards the collapse
Pleural effusion	X-ray finding of obscure or disappearance of costophrenic angle, obscured ipsilateral diaphragm
SIRS	(1) Core body temperature > 38 °C or < 36 °C
	(2) HR > 90 bpm, in cases of atrial arrhythmia, ventricular rate > 90 bpm; exclude when used medications that may affect heart rate
	(3) RR > 20 bpm, or PaCO2 < 32 mmHg (4.2 kPa), or urgent mechanical ventilation used
	(4) WBC > 12,000 or < 4000/μL
Sepsis	(1) Positive microbiologic culture from blood, or definite tissue infection, presence of abscess
	(2) Meets at least 2 SIRS definitions
ALI/ARDS	(1) Lung injury of acute onset (within 1 week or progressive)
	(2) Hypoxemia, PaO2/FiO2 ≤ 300/200 mmHg
	(3) X-ray showing obscured bilateral lobes which cannot be explained by effusion, atelectasis, or nodules
	(4) Respiratory failure that cannot be explained by heart failure or hypervolemia

*PaO2* partial pressure of oxygen, *FiO2* fractional inspired oxygen concentration, *HR* heart rate, *RR* respiratory rate, *WBC* white blood cell, *SIRS* systemic inflammatory response syndrome, *ALI* acute lung injury, *ARDS* acute respiratory distress syndrome

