### Inclusion and exclusion criteria

The inclusion criteria are as follows: (1) age ≥ 70 years, (2) elective surgery, (3) American Society of Anesthesiologists (ASA) classification I–II, (4) body mass index (BMI) ≤ 35 kg/m^2^, (5) provision of signed informed consent.

The exclusion criteria include patients who (1) require emergency surgery; (2) have anticipated difficult intubation; (3) have a broken or unstable cervix; (4) have laryngeal disease; (5) are at high risk of aspiration (gastroesophageal reflux disease, full stomach); (6) are unable to cooperate for any reason, such as inability to speak or understand, mental disease, or inability to go to the clinics; (7) have taken experimental drugs in the preceding 3 months or joined another clinical trial; (8) did not provide informed consent or have withdrawn consent; (9) are evaluated by the investigators as unsuitable for this trial.

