### Blinding, randomization, and allocation concealment

Given the nature of the intervention, blinding of caregivers or patients is not possible. However, investigators responsible for data collection and statisticians will be blinded to the study arms.

Random numbers and group allocations are generated with a 1:1 ratio and stratified according to PPC risk scores (listed in Table 2) by a central randomization system known as an interactive web response system (IWRS) developed by Beijing Blue Balloons Technology Company Limited (http://www.blueballon.cn). Allocations generated by the IWRS will be stored in opaque and numbered envelopes. Participants will be given a randomization number by the designated anesthesiologist and will be allocated according to indications inside that numbered envelope. If participants decide to withdraw after assignment, their clinical information will not be used in this trial, but their assigned random number will still be retained.

**Table 2 Tab2:** PPC risk index

Independent risk factors	Risk score
Age > 70 years	1
Cough and sputum production	1
Diabetes	1
Smoker (or patient quit within the past 6 months)	1
COPD	1
BMI > 27 kg/m^2^	1
FEV1 < 80% and FEV1/FVC < 70%	2

*COPD* chronic obstructive pulmonary disease, *BMI* body mass index, *FEV1* forced expiratory volume in 1 s, *FVC* forced vital capacity

In emergent cases when the LMA or the ETI tube cannot be placed successfully after multiple attempts, anesthesiologists may change the ventilation method or administer different treatments according to their best clinical judgement, and the patient will be excluded from the trial.

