**Fig. 2 Fig2:**
[figure not shown]
Standard Protocol Items: Recommendations for Interventional Trials (SPIRIT) figure for the POLMA-EP trial

Upon arrival, a series of baseline information will be collected, including the patient’s demographics, cause of hospitalization, elective surgery type, medical history, anaphylactic history, and co-morbidities and concomitant medication. Physiological parameters will also be collected, including blood pressure (BP), heart rate (HR), respiratory rate (RR), core body temperature (or axillary temperature + 0.5), ASA classification level, and risk for PPCs. The patient’s cardiovascular, neurological, respiratory, endocrine, and urinary functions will be evaluated and recorded. Laboratory tests including routine blood test, blood gas analysis, and pulmonary function indicators such as vital capacity (VC), forced vital capacity (FVC), forced expiratory volume in 1 s (FEV1), and peak expiratory flow (PEF) will also be measured and documented.

On the day of surgery, anesthetic and surgical recording will also be completed. This will include anesthesia type and duration, mechanical ventilation length, surgery time, PACU stay, blood products (red blood cells/plasma/platelets/fresh frozen plasma/albumin) transfusion, fluid infusion (crystalloid solution and artificial colloids), amount of bleeding, intubation type, times of attempts, ventilation mode, positive end-expiratory pressure (PEEP), tidal volume, types and dosage of anesthetic drugs, and ICU admission and stay.

The PPC level, routine blood tests, blood biochemistry, and blood gas analysis of each patient are evaluated at days 1, 3, and 7 and before discharge. Before discharge, important examinations such as pulmonary radiography and sputum and blood cultures will be completed and recorded. For PPCs, treatments including medication (drug name and dose) and mechanical ventilation (mode, duration, and other parameters) will be documented. In cases of death, the time, cause, and relativity to surgery or anesthesia will be evaluated and recorded.

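### Table 3 counts cough, cough with sputum and hypoxaemia as PPCs without requiring them to be new or worse, so symptoms present before surgery can enter the primary outcome

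*Protocol article*

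**What the plan says.** **Who is in the trial.** Randomisation is "stratified according to PPC risk scores (listed in Table 2"). One scored item there is "Cough and sputum production"; COPD, smoking and reduced spirometry also score. Under Inclusion and exclusion criteria, the respiratory and airway exclusions nearest to this are "4) have laryngeal disease; (5) are at high risk of aspiration (gastroesophageal reflux disease, full stomach"). Nothing there removes patients with chronic cough, sputum, COPD or a smoking habit. Entry is limited to ASA I–II, and the investigator may exclude a patient judged unsuitable.

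**What counts as an event.** "The primary outcomes are the incidence of PPCs (diagnostic criteria shown in Tables 3 and 4) and perioperative mortality rate". In Table 3 only grade 0 is labelled "No pulmonary complications", and no higher threshold for an event is stated. Grade 1 reads "Any one of the following: cough, minor lung atelectasis (no obvious cause), dyspnea (no obvious cause"). Grade 2 begins "Cough and sputum production (no obvious cause), bronchospasm (new-onset asthma or exacerbation of existing asthma that requires treatment") and also lists hypoxaemia on room air (SpO2 < 90% or PaO2 < 60 mmHg).

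**When it is assessed.** PPC level is graded on days 1, 3 and 7 and before discharge (Data collection and follow-up). The baseline data include medical history, a respiratory evaluation, the PPC risk, and "Laboratory tests including routine blood test, blood gas analysis, and pulmonary function indicators". The text mentions no pre-operative PPC grade and no rule for setting aside symptoms already present.

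**The concern.** The same symptom, in nearly the same words, is a baseline stratification item and an outcome item. A patient with a daily cough who is randomised and still coughs on day 1 meets the wording of grade 1, whichever airway device was used.

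Where a time condition was wanted, the tables contain one. Bronchospasm must be new or an exacerbation, the pneumonia infiltrate must be new or progressive, and ALI/ARDS must have an acute onset. Cough, cough with sputum and hypoxaemia have none. With 17 centres, each assessor has to decide alone whether a patient's usual cough scores.

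If such symptoms are counted, patients whose event status cannot depend on the device are added to the numerator of both arms. The reported incidence then no longer describes complications of surgery, and the risk ratio moves towards 1. The planning rates of 15% and 10%, by contrast, are framed as patients developing PPCs.

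**Working it through.** **1. The definitions side by side**

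| Item | Condition on newness or cause |
|---|---|
| Cough (Table 3, grade 1) | none |
| Cough with sputum (Table 3, grade 2) | no obvious cause; nothing on newness |
| Hypoxaemia (Table 3, grade 2) | none |
| Bronchospasm (Table 3, grade 2) | new or exacerbated |
| Pneumonia (Table 4) | new or progressive infiltrate |
| ALI/ARDS (Table 4) | acute onset |

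The cause qualifier on grade 2 may remove a productive cough explained by known COPD or smoking. The patient still has a cough, which is grade 1 without any qualifier.

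**2. Inputs for the size**

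- New-onset PPC rates: p = 15% (ETI) and 10% (LMA), from Sample size estimations.
- Analysed patients: 3,000 × (1 − 0.10) = 2,700 per arm, from the same section.
- Significance level: 0.025 two-sided, the adjusted level that Statistical analysis gives when two χ² tests are performed; there are two primary outcomes. Results at 0.05 are shown as well.
- Baseline prevalence b of an item that Table 3 would count: **not in the protocol; assumed, range 0% to 30%**.

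The protocol's own sample-size figure (2,584 before attrition) does not follow from its stated inputs: effect size 0.09, 2 degrees of freedom, α = 0.05 and 90% power give 1,563. That is a separate matter, and nothing below uses 2,584.

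**3. Formulas**

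- Counted rate in an arm = b + (1 − b)p. This takes the literal reading in full: every patient with the symptom before surgery is counted. If only some are counted, b is correspondingly smaller.
- Risk ratio (RR) = counted LMA rate / counted ETI rate.
- Share of counted events that pre-date surgery = 2b / (sum of the two counted rates).
- Power = Φ(|difference| / SE − z), with SE = √[(p₁(1 − p₁) + p₂(1 − p₂)) / 2,700] and z = 2.241 for 0.025.

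**4. Example, b = 10%**

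- ETI: 0.10 + 0.90 × 0.15 = 0.235. LMA: 0.10 + 0.90 × 0.10 = 0.190.
- RR = 0.190 / 0.235 = 0.81. Difference = 0.045.
- Share = 0.20 / 0.425 = 47%.
- SE = √[(0.1798 + 0.1539) / 2,700] = 0.01112. Then 0.045 / 0.01112 − 2.241 = 1.81, so power = 96%.

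**5. Results**

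| b (assumed) | ETI | LMA | RR | Share pre-dating surgery | Power at 0.025 | Power at 0.05 |
|---|---|---|---|---|---|---|
| 0% | 15.0% | 10.0% | 0.67 | 0% | >99% | >99% |
| 5% | 19.25% | 14.5% | 0.75 | 30% | 99% | 99.7% |
| 10% | 23.5% | 19.0% | 0.81 | 47% | 96% | 98% |
| 15% | 27.75% | 23.5% | 0.85 | 59% | 91% | 95% |
| 20% | 32.0% | 28.0% | 0.875 | 67% | 83% | 89% |
| 30% | 40.5% | 37.0% | 0.91 | 77% | 65% | 75% |

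The estimate is distorted well before power is. At b = 10% the trial keeps 96% power, but a one-third risk reduction appears as one of about a fifth.

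**The case against.** **The outcome is called an incidence of postoperative complications, time of PPC onset is a secondary outcome, and the sample-size text speaks of patients who develop PPCs.** This stands as evidence of intent. A reader might infer that pre-operative symptoms necessarily become events; the protocol does not support that, because an assessor may well discount them. The supportable statement is that they can be counted, since the diagnostic criteria as printed give no rule against it.

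**The cause qualifier covers chronic productive cough.** It does so in part, for grade 2 only. It concerns cause rather than newness, and it is not attached to grade 1 cough.

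**ASA I–II entry and investigator discretion limit the number affected, above all for hypoxaemia.** This is fair. The protocol gives no prevalence, so the rows at 20% and 30% show sensitivity, not expectation. The point rests mainly on cough.

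**Randomisation is stratified by a score containing this symptom.** This also stands. A reader might infer a bias in favour of one device, but expected counts are equal in the two arms and the effect is dilution. Nor may one infer that the trial is underpowered: on these assumptions power at 0.025 stays above 90% up to about b = 15%.

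**PPC level is graded 0 to 4, so a patient who coughs at baseline can still differ between arms at grades 3 and 4.** This is correct. The claim that high-risk patients can show no benefit would hold only for an analysis of any grade against none.

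**The full protocol, the case report form or the schedule in Fig. 2 may deal with this.** That is possible; the figure could not be read here. But the article prints the outcome criteria in full, with time conditions on some items and not on these.

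**Conclusion.** The point holds in limited form. As printed, Table 3 allows cough, cough with sputum and hypoxaemia that were present before surgery to be counted as primary-outcome events, in a population whose stratification score anticipates the first two. The consequences are an inflated incidence and an effect diluted towards no difference, with no tilt towards either arm.

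The size depends on an assumed prevalence and on every such symptom being counted. On those terms the RR moves from 0.67 to 0.75, 0.81 and 0.875 at b = 5%, 10% and 20%, and power at 0.025 is about 96%, 91% and 83% at b = 10%, 15% and 20%. If assessors already discount pre-existing symptoms, the dilution shrinks. What then remains is inconsistency between centres, because the rule is unwritten.

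**What to change.** Add one sentence to the primary-outcome definition: an item in Table 3 or Table 4 counts as a PPC only if that item was absent before surgery, or is worse than at the pre-operative assessment.

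Apply it **item by item**. A rule that the post-operative grade must exceed the baseline grade would conflict with it. A patient with a baseline productive cough (grade 2) who develops new bronchospasm (also grade 2) is an event under the item rule and would be missed under the grade rule.

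The baseline information largely exists: the Table 2 cough-and-sputum item, the respiratory history and evaluation, and the baseline blood gas. It can be used for patients already enrolled. For those still to come, record each Table 3 symptom at the pre-operative assessment. Recruitment is under way, so fix the rule, including what counts as worse, before unblinding.

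Cost: one sentence and a short case-report-form entry, with no new test and no change to eligibility. The counted incidence will be lower than the literal definition gives. For patients enrolled before symptoms were recorded item by item, some judgement about worsening is unavoidable, notably for a dry cough, which the Table 2 item does not separate out.

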**Methods/design:**

In this multi-center, randomized, parallel clinical trial, a total of 6000 elderly patients, aged ≥ 70 years, with an American Society of Anesthesiologists classification level of 1–2 and a body mass index ≤ 35 kg/m^2^, undergoing elective surgery will be enrolled and randomized into the LMA or the ETI group. Both groups will receive usual perioperative care except for the adoption of LMA/ETI. Primary outcomes are the occurrence of PPCs and patients’ perioperative mortality rates. Ease of intubation, anesthetics consumption, treatment for PPCs, duration of surgery, anesthesia recovery time and performance, time of PPC onset, postanesthesia care unit stay, intensive care unit admission and stay, in-hospital days, re-admission rates, hospitalization cost, and patients’ satisfactory scores will be secondary outcomes. Follow-up will be conducted through phone-call visits until 12 weeks after discharge.

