A brief summary of discharge will include discharge diagnosis, hospitalization stay, ICU admission and length, and hospitalization fee. Follow-up will be done on day 28 ± 7 after surgery. Apart from the PPC score, a self-evaluating questionnaire covering overall health, daily activity level, limitations during work, pain, energy, social activity, passive emotions, personal issues, accompanying pulmonary diseases, and overall satisfaction will be completed. Another follow-up will take place on day 84 ± 7 post surgery. The follow-up will be in the form of phone-call visits by designated allocation-blinded clinicians.

Data will be collected on paper case report forms (CRFs) by nurses or clinicians blinded to group allocation and then collected onto electronic CRFs (eCRFs) by trained assistants. The eCRF is a restricted online system that is capable of alerting information inconsistencies, missing data, and atypical errors. The database will be available for editors and peer reviewers when required.

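### Tables 3 and 4 jointly define the primary outcome but classify the same patient differently, and cough alone, not necessarily new, counts as a PPC

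*Protocol article*

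**What the plan says.** Under Primary outcomes the protocol article states: "The primary outcomes are the incidence of PPCs (diagnostic criteria shown in Tables 3 and 4) and perioperative mortality rate". It does not say which table governs, how the two combine, or from which grade a patient is an event.

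Table 3 grades PPCs from 0 to 4. Grade 0 is the only grade that denotes absence of a complication. Grade 1 is "Any one of the following: cough, minor lung atelectasis (no obvious cause), dyspnea (no obvious cause". The qualifier about cause follows atelectasis and dyspnea, not cough.

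Table 4 gives diagnostic criteria for six conditions: pneumonia, atelectasis, pleural effusion, SIRS, sepsis and ALI/ARDS. Effusion is "Pleural effusion (that requires drainage" in Table 3 but "X-ray finding of obscure or disappearance of costophrenic angle, obscured ipsilateral diaphragm" in Table 4.

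Table 2, the risk index used for stratification, lists "Cough and sputum production" as a baseline factor. The Background names less airway irritation as an advantage of the LMA. The sample size section assumes a fall in PPC incidence from 15% to 10% without naming a table or a grade.

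**The concern.** A binary primary outcome needs one rule that sorts each patient into event or non-event. Here two lists are both called diagnostic criteria, they overlap only in part, and where they overlap they conflict. Sites and assessors could apply either one in good faith, and the event count would depend on which they chose.

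Cough adds a second problem. The protocol's own rationale leads one to expect that the device changes cough through irritation of the airway. If cough alone is an event, a difference in PPC incidence may reflect irritation and not lung complications. If cough is common and equal in both arms, it dilutes a real difference. Blinded data collection does not help with either, because a true device effect on cough is not an assessment bias.

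**Working it through.** **1. The tables side by side**

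| Patient | Table 3 | Table 4 |
|---|---|---|
| Cough only | Grade 1 | Not an event (cough is only a supporting sign of pneumonia) |
| Effusion on X-ray, not drained | No grade by itself | Event |
| Infiltrate on X-ray with one further sign | Grade 3, suspected pneumonia | Not pneumonia (two of three signs needed) |
| Abnormal chest sign with temperature above 37.5, no X-ray | Grade 2, atelectasis | Not established (criteria mainly X-ray) |
| SIRS without pulmonary signs | No entry | Event |

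Sepsis and ALI/ARDS also have no entry of their own in Table 3. Conversely, cough, dyspnea, bronchospasm, hypoxemia, hypercapnia, pneumothorax and short ventilation are in Table 3 only.

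**2. The plan's own figure**

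The only incidence figures are 15% v 10%. With 3,000 × 0.9 = 2,700 evaluable patients per arm, that difference has power above 99.9% at two-sided alpha 0.05. (The stated sample size inputs do not reproduce the stated 2,584. That is a separate matter, and nothing here depends on it.)

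**3. Illustration: cough differs, everything else equal**

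Inputs from the document: 3,000 per arm, 10% attrition, alpha 0.05. Assumed: other PPCs 12.5% in both arms (the midpoint of 15% and 10%), and cough rate c among patients without another PPC.

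Any PPC = 1 − (1 − 0.125)(1 − c)

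Power = Φ[(d − z·SE0)/SE1], where d is the difference, SE0 = √(2·p̄(1 − p̄)/2,700) and SE1 = √([p1(1 − p1) + p2(1 − p2)]/2,700).

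For 10% v 7%: p1 = 1 − 0.875 × 0.90 = 0.2125, p2 = 1 − 0.875 × 0.93 = 0.18625, d = 0.02625, SE0 = 0.01087, SE1 = 0.01087. Power = Φ[(0.02625 − 1.96 × 0.01087)/0.01087] = Φ(0.454) = 0.675.

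| Cough, ETI v LMA (assumed) | Any PPC | Significant at 0.05 | At 0.025 |
|---|---|---|---|
| 10% v 9% | 21.3% v 20.4% | 12% | 7% |
| 10% v 8% | 21.3% v 19.5% | 36% | 26% |
| 10% v 7% | 21.3% v 18.6% | 67.5% | 57% |
| 15% v 10% | 25.6% v 21.3% | 97% | 94% |

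The 0.025 column is shown because the Statistical analysis section lowers the threshold to that value when two χ² tests are performed.

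**4. Illustration of the opposite risk: cough equal, other PPCs truly 15% v 10%**

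Any PPC = p + (1 − p)c, with 2,700 per arm and alpha 0.05.

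| Cough in both arms (assumed) | Any PPC | Power |
|---|---|---|
| 10% | 23.5% v 19.0% | 98% |
| 20% | 32.0% v 28.0% | 89% |
| 30% | 40.5% v 37.0% | 75% |
| 40% | 49.0% v 46.0% | 60% |

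**The case against.** The strongest defence is that Table 3 grades severity while Table 4 supplies the criteria. That does not rescue the text: the outcome sentence calls both tables diagnostic criteria, their shared items conflict, and their item lists differ. If either table were sufficient, cough would still count.

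A second defence is that an analysis plan commonly fixes the counting grade and the window. That is fair, and their absence alone would not be a finding. The finding is the contradiction in the text shown.

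Several stronger readings are tempting, and the documents do not support them:

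- A reader might infer that the LMA will win on cough alone. The Background supports only a direction. No cough rate is given for either device, and with a gap of one or two points the chance of a significant result is modest.
- A reader might infer that pre-existing cough biases the result towards the LMA. Cough with sputum enters the stratified risk score, so it should be roughly balanced. The expected effect is dilution.
- A reader might conclude that nothing in the tables has to be new. That is true of cough, but bronchospasm, pneumonia and ALI/ARDS carry onset or progression wording.
- A reader might say that 15% v 10% fits neither table. The sample size section is silent on this, and silence does not show a mismatch.
- A reader might want SIRS removed. The Background names SIRS within the PPC concept. Its inclusion is the authors' choice, and the defect is only that Table 3 has no place for it.

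**Conclusion.** The definition is wrong as written and must be settled before unblinding. The conflict between the tables, and the status of cough alone as an event that need not be new, follow from the text and need no assumption. Together they can change the primary event count.

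The size of the effect on the trial's conclusion cannot be derived from the document. Under the assumed rates above, the chance that cough alone yields a significant PPC difference runs from 12% to 97% at alpha 0.05. Equal cough of 10% to 40% lowers power for a true 15% v 10% difference from above 99.9% to between 98% and 60%. These figures show what could happen and are not forecasts.

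Two minor points also need reconciling. Table 3 describes hypercapnia as "caused by medication or over-ventilation", although over-ventilation lowers carbon dioxide. The Abstract says "Follow-up will be conducted through phone-call visits until 12 weeks after discharge", whereas Data collection and follow-up says "Another follow-up will take place on day 84 ± 7 post surgery". Twelve weeks is 84 days, so the two differ by the length of the postoperative stay. Neither point decides which table governs.

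**What to change.** Before unblinding, amend the protocol, the case report form guidance and the analysis plan to:

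- state one governing event definition, with one criterion each for effusion, pneumonia and atelectasis;
- say whether and how SIRS, sepsis and ALI/ARDS count, and give them a grade if they do;
- require cough, and cough with sputum, to be new or worsened since baseline. This matters at grade 2 as well, because cough with sputum sits there and a cut-off at grade 2 alone would not remove airway symptoms;
- state the grade at which a patient is an event, so that isolated cough does not decide the primary result. Pre-specify grade 1 or above (or grade 2 or above, if grade 1 stays in the primary outcome) and the ordinal grade as secondary analyses;
- name one assessment window, the same in both arms and compatible with the radiograph planned before discharge. A window that closes at day 7 or discharge, whichever is first, could miss that radiograph in longer stays and would vary with length of stay;
- say which definition the 15% v 10% assumption refers to;
- correct the two minor points above.

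The cost is mainly wording, since PPC level, laboratory tests and radiography are already to be recorded. Recruitment was ongoing at publication. The downside is a possibly lower event rate. No rate for a stricter definition is given. With 2,700 per arm and alpha 0.05, an assumed 6% v 4% has 92% power and an assumed 3% v 2% has 65%, so the sponsor should check the expected rate before choosing the cut-off.

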Geriatric patients often have limited mouth opening and cervical movement, poor cardiovascular tolerance, and altered pharmacokinetics. Under these circumstances [5], a laryngeal mask airway (LMA) is considered a good alternative to endotracheal intubation (ETI) because of its advantageous characteristics such as ease of insertion [13], less irritation to the airway, less reliance on muscle relaxant, and better patient comfort [14]. As a supraglottic airway device, however, it does not separate the trachea from the esophagus; therefore, the LMA is associated with higher incidence of aspiration of gastric contents, especially in susceptible patients with a history of gastroesophageal reflux disease [15]. Moreover, the LMA is not recommended for use in lengthy surgery, morbidly obese patients, or certain other types of surgeries in which more control of the breathing (e.g., heart, lung, and brain surgeries) [16] is required. Therefore, the LMA and ETI both have major roles in daily anesthetic practice, and their influences on PPCs under various circumstances are inevitable topics for question.

In contrast to the popularity of LMA or ETI usage in geriatric surgeries, research evidence about their effect on PPCs is scarce and incomprehensive. Our group published a retrospective single-center study that compared LMA and ETI use in geriatric patients who underwent elective abdominal surgery, and we found that, among those who were transferred into the intensive care unit (ICU), the LMA group was associated with lower incidence of atelectasis and pulmonary embolism [17]. To better clarify whether the use of LMA is superior to ETI for elderly surgical patients and provide sufficient evidence for clinical decision-making, we have designed the current large-scale, randomized, controlled clinical trial. Its rationale, design, and protocol will be described in this paper.

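### Table 3 words the grade 2 bronchospasm item only in terms of asthma, so treated bronchospasm in COPD falls outside it and can be lost, graded lower or classified differently between sites

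*Protocol article*

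**What the plan says.** Under Primary outcomes the protocol article states: "The primary outcomes are the incidence of PPCs (diagnostic criteria shown in Tables 3 and 4) and perioperative mortality rate". Table 3 grades complications from 0 to 4, and Table 4 defines individual diagnoses.

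- **The bronchospasm item (Table 3, grade 2):** "bronchospasm (new-onset asthma or exacerbation of existing asthma that requires treatment". Table 4 covers pneumonia, atelectasis, pleural effusion, SIRS, sepsis and ALI/ARDS. It has no entry for bronchospasm, wheeze or COPD exacerbation.
- **Neighbouring items:** grade 1 is "Any one of the following: cough, minor lung atelectasis (no obvious cause), dyspnea (no obvious cause"; grade 2 also contains "hypoxemia (SpO2 < 90% or PaO2 < 60 mmHg while breathing air".
- **Population:** COPD (spelled out under Table 2 as "chronic obstructive pulmonary disease") scores one point in the PPC risk index by which randomization is stratified. It is not among the exclusion criteria.
- **Device difference:** the Background lists "less irritation to the airway" among the advantages of the LMA.
- **Data collection:** PPC level is assessed on days 1, 3 and 7 and before discharge. For PPCs, "treatments including medication (drug name and dose" are recorded.

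**The concern.** The definition is narrower than the population. The trial enrols COPD patients and treats COPD as a risk factor for the outcome, but its bronchospasm item names one underlying disease only. The same clinical event, bronchospasm needing treatment, then scores grade 2 if the clinician calls it asthma and possibly grade 0 or 1 if the clinician calls it COPD.

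At stake are the validity of a primary outcome component, the grade assigned, and consistency across 17 centers. The secondary outcomes on treatment for PPCs and time of PPC onset inherit the classification.

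**Working it through.** The document gives no figure for bronchospasm, so the main check sets the wording of the items side by side. Take a COPD patient with new wheeze that is treated after surgery, and ask which Table 3 item counts the event on a literal reading.

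| Item (grade) | Limiting condition in Table 3 | Counts this patient? |
|---|---|---|
| Bronchospasm (2) | asthma, new or exacerbated | No |
| Cough (1) | none | Yes, if there is cough; grade 1 |
| Dyspnea (1) | no evident cause | Doubtful: recognised bronchospasm is a cause |
| Cough with sputum (2) | no evident cause | Doubtful, same reason |
| Hypoxemia (2) | measured on air | Yes, if present and measured so |
| Hypercapnia (2) | attributed to drugs or ventilation | Doubtful |
| Ventilation under 48 h (3) or over 48 h (4) | none on cause | Yes, if ventilated |

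Treated wheeze with none of the other signs scores 0. With cough alone it scores 1. Labelled asthma, the same event scores 2. The article does not say which grade makes a PPC event. If any grade counts, only the cases scoring 0 are lost; if grade 2 were the cut-off, the cough-only cases would be lost too.

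For a patient with neither disease whose bronchospasm is set off by the device, the result depends on whether new-onset asthma is read as a diagnosis or as loose wording for any new bronchospasm. The text supports either reading.

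**Could lost events threaten power?** Inputs from Sample size estimations: 3,000 per group, 10% attrition, PPC rates of 15% (ETI) and 10% (LMA). Evaluable per group: 3,000 × 0.90 = 2,700. (The stated requirement of 2,584 is not used. It does not follow from its own inputs: effect size 0.09, 2 df, α 0.05 and 90% power give 12.654 / 0.09² = 1,563. That is a separate matter.)

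Power = Φ[(p₁ − p₂ − 1.96·s₀) / s₁], with s₀ = √(2p̄(1 − p̄)/n), s₁ = √((p₁(1 − p₁) + p₂(1 − p₂))/n) and p̄ = (p₁ + p₂)/2.

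As planned: s₀ = 0.00900 and s₁ = 0.00898, so (0.05 − 1.96 × 0.00900)/0.00898 = 3.61 and power is 99.98%.

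The shares of events missed below are assumptions, since the document gives none.

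| Assumed loss | Rates compared | Power |
|---|---|---|
| 5% of events, both arms | 14.25% vs 9.5% | 99.97% |
| 10%, both arms | 13.5% vs 9.0% | 99.95% |
| 20%, both arms | 12% vs 8% | 99.84% |
| 0.25 points, ETI only | 14.75% vs 10% | 99.96% |
| 0.5 points, ETI only | 14.5% vs 10% | 99.90% |
| 1 point, ETI only | 14% vs 10% | 99.5% |
| 2 points, ETI only | 13% vs 10% | 93.3% |

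The Statistical analysis section lowers the threshold to 0.025 when two χ² tests are performed. With 2.241 in place of 1.96, the last row becomes (0.03 − 2.241 × 0.00868)/0.00867 = 1.22, or 88.8%. That row is extreme: it loses 2 of 15 points in one arm and none in the other. It would also move the observed risk ratio from 0.10/0.15 = 0.67 to 0.10/0.13 = 0.77.

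**The case against.** Four points can be made for the plan.

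**Other items catch these patients.** This largely stands. Cough has no qualifier, and hypoxemia and ventilation also count, so it would be wrong to say that non-asthmatic bronchospasm cannot be a PPC of grade 2 or above. What remains is the isolated case and the lower grade.

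**New-onset asthma may simply mean new bronchospasm in a patient without asthma.** This stands for device-triggered cases, where the defect is ambiguity and not certain exclusion. It does not help COPD, which fits neither alternative naturally, and it leaves each site to choose its reading.

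**The event is documented as an adverse event, and assessors are blinded.** Adverse event recording protects safety reporting but does not put the event into the primary outcome. Blinding limits labelling that differs by arm, not labelling that differs by site.

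**No bias is shown.** This stands. A reader might infer that irritative bronchospasm is the event closest to the trial's mechanism, so that dropping it pulls the comparison toward no difference. The Background names irritation as one of several LMA advantages and never links it to bronchospasm; the group's earlier study is cited for atelectasis and pulmonary embolism. Nor does under-counting alone shrink the ratio. Expected events are 3,000 × 0.15 = 450 and 3,000 × 0.10 = 300, together 750. Losing 90 of them in the same proportion (54 and 36) leaves 396 and 264: the ratio is still 0.67, and the difference falls from 5.0 to 4.4 points. Attenuation of the ratio needs the missed events to depend on the device more than other PPCs do, and the document gives no support for that.

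**Conclusion.** The point holds as a defect of definition. A stated criterion of the primary outcome literally excludes treated bronchospasm in a group that the trial enrols, and leaves device-triggered bronchospasm without asthma open to either reading. The consequences are loss of isolated cases, lower grading of others, and dependence on the label used at each site.

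Its size cannot be derived. A reader might assume that 5–15% of 6,000 patients have COPD (300–900) and that 5–10% of these need treatment for bronchospasm (15–90 events), which is 2–12% of the 750 expected. Both rates are assumptions. The range also presumes that no such patient qualifies through another item, and the restriction to ASA I–II may favour the low end. It should not be quoted as the size of the problem.

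No direction of bias follows from the document. Power stays at or above 93% at α 0.05 in every scenario above, and only the extreme one-sided loss falls below 90% at 0.025. The matter is therefore endpoint validity and consistency, not mainly power.

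**What to change.** Reword the grade 2 item in Table 3 as: *new or worsened bronchospasm or wheeze, compared with baseline, in the postoperative assessment window, that requires treatment, whatever the underlying disease*.

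- Record asthma, COPD or neither on the CRF as a descriptor, not as a condition for counting.
- Have the blinded assessor judge the event. Do not derive it from drug records: the Discussion says that anticholinergics and steroids may be given prophylactically, and the medication record described under Data collection and follow-up is for PPCs, so it may not hold treatment of an event not classed as one.
- Keep the item to the postoperative window, so that intraoperative bronchospasm is not drawn into a postoperative outcome.
- Recruitment is under way, so make and date the change blind to outcome by arm.

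The cost is one line in Table 3, one CRF item and a note to sites, with no new procedure for patients. Slightly more events will be counted. New wheeze has to be compared with the baseline respiratory evaluation already collected, and patients already assessed may need a check against recorded data.
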